**Enrollment**						
	Eligibility screen	✓^a^	–^b^	–	–	–
	Informed consent	✓	–	–	–	–
	Allocation	–	–	✓	–	–
**Intervention**						
	*Inroads* ^c^	–	–	✓	✓	–
	Control	–	–	✓	✓	–
**Assessments**						
	Alcohol Use Disorder Identification Test	✓	–	–	✓	✓
	Generalized Anxiety Disorder-7	✓	–	–	✓	✓
	Mini-Social Phobia Inventory	✓	–	–	–	–
	National Institute on Drug Abuse quick screen	✓	–	–	–	–
	Psychosis Screening Questionnaire	✓	–	–	–	–
	Alcohol Outcome Expectancies tension-reduction scale	–	✓	–	✓	✓
	Brief Young Adult Alcohol Consequences Questionnaire	–	✓	–	✓	✓
	Depression and Anxiety Stress Scale	–	✓	–	✓	✓
	Drinking Motives Questionnaire-Revised	–	✓	–	✓	✓
	Emotion Regulation Questionnaire	–	✓	–	✓	✓
	Life Events Checklist for Diagnostic and Statistical Manual of Mental Disorders, Fifth Edition (DSM-5)	–	✓	–	✓	✓
	Post-Traumatic Stress Disorder symptom checklist for DSM-5	–	✓	–	✓	✓
	Self-Compassion Scale-Short Form	–	✓	–	✓	✓
	Sheehan Disability Scale	–	✓	–	✓	✓
	Social Phobia Scale and Social Interaction Anxiety Scale-Short forms	–	✓	–	✓	✓
	Substance Use Risk Profile Scale	–	✓	–	✓	✓
	Treatment Acceptability Questionnaire	–	–	–	✓	–
	Timeline Follow-Back	–	✓	–	✓	✓
	Working Alliance Inventory-Short Form	–	–	–	✓	–

^a^Indicates that enrollment, intervention delivery and/or assessments occurred at these time points.

^b^Indicates that enrollment, intervention delivery and assessments were not relevant at these time points.

^c^*Inroads* intervention includes 5 modules which are delivered over 5 weeks, with flexibility in module completion provided up until t_2_ (8-week post- baseline assessment).

#### Secondary Outcomes

Module completion, time spent, rate of completion, and number and duration of therapist contacts via email, chat, and phone will be recorded to measure treatment retention and dose. Frequency of binge drinking (past month consumption of ≥5 standard drinks on 1 occasion) will be calculated from alcohol consumption data collected using the TLFB procedure [53,54]. Symptoms specific to social anxiety will be assessed using the 12-item Social Phobia Scale and Social Interaction Anxiety Scale-short forms [58]. Items are scored on a 5-point Likert-type scale from 0 “Not at all characteristic or true of me” to 4 “Extremely characteristic or true of me.” Total scores range from 0 to 48, with higher scores indicating higher levels of social anxiety. Symptoms of anxious arousal and depression will be assessed using the 21-item anxiety and depression subscales of the Depression and Anxiety Stress Scale [59]. Items are rated on a 4-point scale (0-3), summed and doubled for each subscale. Subscale scores range from 0 to 42, with higher scores indicating greater severity of emotional symptoms. Overall, functional impairment and quality of life will be assessed by the Sheehan Disability Scale [60] *.* Participants rate the extent to which their work, social life/leisure activities, and home life/family responsibilities are impaired by their symptoms on a 10-point visual analog scale. Higher numbers indicate greater impairment. The 3 items may be summed into a single dimension of global functioning impairment that ranges from 0 “unimpaired” to 30 “highly impaired.” The 28-item Drinking Motives Questionnaire-Revised [61] will be used to assess alcohol use motives across 5 subscales: social, coping-anxiety, coping-depression, enhancement, or conformity. Each item is rated on a 5-point Likert scale ranging from 1 “almost never/never” to 5 “almost always/always.” Subscales are scored as the average across the items within a scale, which allows a direct comparison across subscales. Positive alcohol expectancies will be assessed by the 17-item alcohol tension-reduction expectancies scale [62]. Each item is scored from 0 “not at all important” to 3” very important,” with total scores ranging from 0 to 51. Higher scores indicate greater expectancies regarding the tension-reducing effects of alcohol.

Additional measures will be included to explore secondary research questions, namely (1) Emotion Regulation Questionnaire [63] to assess emotional regulation difficulties; (2) Self-Compassion Scale-Short Form to assess self-compassion [64]; (3) Life Events Checklist for Diagnostic and Statistical Manual of Mental Disorders, Fifth Edition (DSM-5) [65], adapted to assess lifetime exposure to potentially traumatic events; (4) Post-Traumatic Stress Disorder (PTSD) symptom checklist [66] to assess severity of past-month PTSD symptoms according to DSM-5; (5) Working Alliance Inventory-Short Form-revised [67] to assess therapeutic alliance; (6) Treatment Acceptability Questionnaire [68]; and (7) Substance Use Risk Profile Scale [69] to assess personality risk factors. Demographic information including age, sex, education, employment, country of birth, sexuality, geographical location, and treatment use (ie, medication and treatment from health professionals such as psychologists, psychiatrists, counselors, and general practitioners) will also be collected.

#### Inroads Anxiety and Alcohol Use Intervention

The *Inroads* program is a therapist-supported, internet-delivered CBT program aimed at reducing symptoms of anxiety, hazardous alcohol consumption, and alcohol-related harms. It involves 5 sequential modules over a 5-week period that focus on enhancing motivation to change and developing CBT strategies to manage anxiety and hazardous alcohol use. Each module should take approximately 30 min to 45 min to complete, and to allow time for skill practice and consolidation, new modules will become available at a rate of 1 module each week, irrespective of whether the previous module has been completed. Automated email and SMS text message reminders to complete program modules will be provided weekly. Goal setting, planning, and review are completed each module, with new skills being introduced in each module (Table 2).

The content for each module is delivered via written text, images, infographics, and interactive forms, whereby participants are guided to identify their goals recognize their cognitive and/or behavioral responses, and practice CBT skills by working through personal examples. Additional online forms are provided for homework practice. In modules 2, 3, and 4, a brief 3-min animated video illustrates the key skills introduced in the module (module 2: realistic thinking, module 3: strategies to reduce or avoid drinking, module 4: facing fears to overcome anxiety). In addition, as participants work through the program, they follow the stories of 2 characters. This narrative is presented via audio segments (with accompanying text) to illustrate case examples aligned with the key concepts or skills in each module. A 5-item quiz at the end of each module provides the opportunity for participants to test and reinforce their knowledge of the key points.

Therapist support will be provided by a team of trained psychologists, ranging from recent graduates to experienced clinicians, who will receive supervision from experienced clinicians. At the completion of each module, participants will receive an email providing feedback, troubleshooting, and personalized suggestions aligned to module content. In addition, telephone and/or chat sessions following modules 1 (30 min) and 4 (30 min) will focus on motivational enhancement, developing a shared anxiety-drinking problem formulation, troubleshooting, and tailoring behavioral experiments and cognitive therapy exercises. The 5 modules are intended to be completed weekly; however, to allow some flexibility in the rate of completion, postintervention surveys will be administered to all participants 8 weeks after baseline. Participants in the intervention will also be asked to complete another follow-up survey 6 months post baseline.

**Table 2 table2:** New skills introduced in each module of the *Inroads* program.

Modules	Skills learned
Module 1	Normative feedback about alcohol use; understanding motives for change and the interrelationship between anxiety and alcohol use; psychoeducation regarding the cognitive, physiological, and behavioral aspects of anxiety and alcohol use; goal setting and drinking limits; and emotion surfing to ride out cravings and uncomfortable feelings
Module 2	Understanding the ABC^a^ model and cognitive therapy targeting anxious thoughts
Module 3	Cognitive behavioral therapy strategies for sticking to drinking limits, cognitive therapy targeting positive alcohol expectancies (ie. ‘drinking thinking’), assertiveness, and handling group dynamics
Module 4	Understanding avoidance and anxiety and graded behavioral experiments
Module 5	Enhancing social support, longer-term goal setting, and relapse prevention

^a^ABC: Refers to activating event or objective situation, belief, and consequences.

#### Assessment and Alcohol Information Control

Participants in control condition will receive assessment followed by an online information pamphlet outlining the effects of alcohol and risks of overuse, the Australian National Health and Medical Research council’s recommended guidelines for alcohol consumption, and a list of links to national telephone helplines and alcohol information websites. The information pamphlet will be available for immediate download and will also be emailed to them. Past research demonstrates that answering detailed questions about drinking alters subsequent self-reported behavior, particularly among young adult samples [70-72], and thus, it is expected that the assessment procedures in combination with information provision will lead to a modest decrease in alcohol consumption in the control group. By using an alcohol-only control condition, the *Inroads* integrated intervention can be compared with current recommendations for comorbidity management, which state that alcohol use problems should be addressed before co-occurring conditions such as anxiety [73]. Participants in the control group will be informed that they will be recontacted in 8 weeks and 6 months for follow-up surveys, and after completion of the final survey, they will be offered the *Inroads* program.

### Safety Protocol

Before consenting to the study, the information statement will provide all participants with a list of crisis and support services. At entry to the study, participants will be screened for risk of complicated alcohol withdrawal and active suicidal ideation in the past 2 weeks, and those who screen positive will be referred to appropriate support services. For participants allocated to the *Inroads* program, the project psychologists will monitor symptoms during phone, email, and/or chat contact and via review of content submitted online. The Web-based program will provide links for participants to request additional support from the project psychologists via phone or chat room. Psychologists will provide up to a maximum of 2 hours of additional phone and/or chat support where required, and in cases where a severe deterioration or safety risk is indicated, participants will be referred to appropriate services for more intensive support. Participants in both conditions will complete assessments 8 weeks and 6 months after baseline, which provides an opportunity for symptom monitoring, and all participants will be provided with a list of support services that can be accessed should they require additional help. In addition, the trial website will automatically detect any English words or phrases entered in the program modules or assessment surveys that are consistent with the vernacular of suicidal ideation [74]. If any words indicative of suicidality are detected, a notification will be sent to the project psychologists, who will manually examine the relevant content. When manual review suggests suicidal ideation, the psychologist will contact the participant to conduct a risk assessment and provide referral to appropriate support services.

### Sample Size

Previous evaluations of brief, multisession, internet-delivered interventions for young adults have indicated an effect size at post intervention of between 0.68 and 0.99 for reduction in the number of drinks consumed [39,75], 0.56 for reduction in alcohol-related consequences [75], and 0.59 for reduction in anxiety symptoms [76]. Optimal Design software [77] was used to calculate the required sample size, taking into account the multilevel analysis with a nested repeated measures design. Using a conservative approach with intraclass correlation coefficient of .55 estimated based on our adult comorbidity trial [37], power calculations indicated a sample size of 90 (45 each group) would be required to detect a moderate effect size of 0.50 between the intervention and control group with power=0.8 and alpha=.05. To allow for data attrition at post assessment, estimated at 35% (n=32/90) [78], a total sample of 122 individuals will be recruited to the study.

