**Methods:**

A randomized controlled trial will be conducted nationally among young Australians (aged 17-24 years) who experience anxiety symptoms and drink alcohol at hazardous or harmful levels. Participants will be individually randomized on a 1:1 basis to receive the *Inroads* intervention or assessment plus alcohol guidelines. Participants randomized to the *Inroads* intervention will receive access to 5 Web-based cognitive behavioral therapy (CBT) modules and weekly therapist support via email and/or phone. The primary outcome assessment will be 8 weeks post baseline, with follow-up assessment 6 months post baseline to determine the sustainability of the intervention effects. Primary outcomes will be the total number of standard drinks consumed in the past month (assessed by the Timeline Follow-Back procedure), severity of alcohol-related harms (assessed by the Brief Young Adult Alcohol Consequences Questionnaire), and anxiety symptoms across multiple disorders (assessed by the Generalized Anxiety Disorder-7). Secondary outcomes will include alcohol outcome expectancies; functional impairment and quality of life; and symptoms of social anxiety, anxious arousal, and depression. Results will be analyzed by intention-to-treat using multilevel mixed effects analysis for repeated measures.

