## Methods

### Study Setting and Design

The study will be conducted nationally across Australia and involves a parallel RCT in which eligible participants will be individually randomized into either (1) the intervention condition (*Inroads* program) or (2) the control condition (assessment plus alcohol guidelines and information). The primary end point will be the posttreatment assessment, conducted at 8 weeks following baseline, with a secondary end point at 6 months after baseline. Figure 1 depicts the study design.

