### Statistical Analysis

Primary analyses will use multilevel mixed effects analysis for repeated measures [79,80], which is a flexible analytic approach for modeling change over time that has emerged as a flexible and rigorous method for analyzing RCT results. The approach has a number of advantages over traditional approaches, including better treatment of missing data and flexible modeling of variance at the individual level, time effects, and the within-subject covariance structure [79,80]. Models will include a random intercept, and preliminary models will be estimated and model fit statistics examined to determine the most appropriate model and covariance structure. All models will use baseline measurements as the reference point to estimate participant-specific starting points and change over time. Intervention condition will be represented by a dummy-coded variable, and the condition by time interaction will be examined to assess between-group differences in treatment response over time. Treatment dose (hours of therapist contact and module completion) will be entered as an independent variable in secondary analyses to examine moderation of treatment effects. For outcomes with evidence of significant intervention effects, Cohen *d* will be calculated from model estimated marginal means and standard errors to determine the size of effect between conditions at the relevant end point. All analyses will be carried out on an intention-to-treat basis, retaining and analyzing all participants in the intervention groups they were originally allocated to. Missing data will be accounted for in all analyses using maximum likelihood estimation, and the impact of missing data on study conclusions will be examined using recommended methods [81]. Data analyses will be conducted using Stata, version 15 [82], with significance levels set at *P*<.05 (95% CI).

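### The 80% power at 90 participants is tied to no named contrast: for the 8-week condition-by-time test as described it is about 70%, and a high ICC is not a safe-side choice for that end point

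*Protocol article*

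**What the plan says.** The Sample Size section of the protocol article reports a calculation in Optimal Design software, "taking into account the multilevel analysis with a nested repeated measures design". Its key input is introduced as follows: "Using a conservative approach with intraclass correlation coefficient of .55 estimated based on our adult comorbidity trial". The result is 90 participants, 45 in each arm, and the claim attached to that number is that it can "detect a moderate effect size of 0.50 between the intervention and control group with power=0.8 and alpha=.05". The section does not say which contrast this refers to, how many waves were entered, or whether the test is one- or two-sided.

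Two other sections say what the power should refer to. Study Setting and Design states: "The primary end point will be the posttreatment assessment, conducted at 8 weeks following baseline". Statistical Analysis describes mixed models with a random intercept, baseline as the reference for change, and a dummy variable for condition, and says that "the condition by time interaction will be examined to assess between-group differences in treatment response over time". It mentions neither baseline as a covariate nor equal baseline means across the arms, and it leaves the final model and covariance structure to be chosen on fit.

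**The concern.** In a repeated-measures design the effect of the within-person correlation on power depends on the contrast. If the waves are averaged, a higher correlation means less new information per wave and more participants. If the follow-up score is compared with baseline or adjusted for it, a higher correlation removes more between-person variation and fewer participants are needed. An ICC can therefore be called conservative only once the contrast is known, and the article does not name it.

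The 80% power at 0.50 is the only precision claim in the article. If it belongs to a different contrast from the one to be tested at 8 weeks, the trial is less sensitive than stated. The label adds to this: a reader will take it that any error in an ICC borrowed from an adult trial lies on the safe side, whereas at 8 weeks a lower correlation among 17- to 24-year-olds would cost power.

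**Working it through.** **Inputs from the article.** Effect d = 0.50, alpha .05, power 0.80, ICC ρ = .55, 45 per group (Sample Size); 1:1 allocation (Abstract, Methods); three waves, at baseline, 8 weeks and 6 months (Measures); primary end point at 8 weeks (Study Setting and Design).

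**Assumptions.** Two-sided test; compound symmetry, which is what a random intercept alone implies; d in units of the single-wave SD; all 90 observed, so that attrition plays no part.

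**Method.** Each contrast is a two-group comparison whose variance is the single-wave variance times a factor v. By the normal approximation, n per group = 2v(1.960 + 0.842)²/d². The totals below use the noncentral t distribution with N − 2 degrees of freedom.

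**Step 1: reproduce the 90.**
- Mean of all three waves: v = (1 + 2ρ)/3 = (1 + 1.10)/3 = .700. Normal: 2 × .700 × 7.849/.25 = 43.95, so 44 per group. Noncentral t: 45 per group, N = 90, power 80.1%.
- 8-week score adjusted for baseline, or baseline means constrained equal: v = 1 − ρ² = 1 − .3025 = .6975. Normal: 43.80, so 44 per group. Noncentral t: 45 per group, N = 90, power 80.2%.

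The figure is reproduced, but by two different tests. A one-sided test of change also gives 90, by the normal approximation. The match therefore does not identify the contrast that was powered.

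**Step 2: the test as most naturally read.** For the unconstrained condition-by-time contrast from baseline to 8 weeks, v = 2(1 − ρ) = 2 × .45 = .900.
- Normal: 2 × .900 × 7.849/.25 = 56.5, so 57 per group, N = 114. Noncentral t: 58 per group, N = 116.
- Power at N = 90: 69.6%.
- Effect detectable with 80% power at N = 90: 0.57.

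If the interaction is instead tested jointly over both follow-ups (2 degrees of freedom) with d = 0.50 at each, power at 90 is about 73% and 80% needs 106.

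**Step 3: direction of the ICC.** Total N for 80% power, with power at N = 90 in brackets:

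| Contrast | ICC .40 | ICC .55 | ICC .70 |
|---|---|---|---|
| 8-week change, v = 2(1 − ρ) | 154 (57%) | 116 (70%) | 78 (86%) |
| 8-week score, baseline-adjusted, v = 1 − ρ² | 108 (73%) | 90 (80%) | 68 (91%) |
| Mean of three waves, v = (1 + 2ρ)/3 | 78 (86%) | 90 (80%) | 104 (75%) |

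In both 8-week rows N falls as the ICC rises. Only in the averaged row, which is not an 8-week comparison, is a higher ICC the cautious choice.

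**The case against.** The strongest objection is that the 70% is conditional. The article leaves the model and covariance structure open, and a condensed article may leave the handling of baseline to the full protocol or analysis plan. If baseline is adjusted for or constrained, the stated 80% is correct at 8 weeks. This stands, and a flat statement that the trial has 70% power would go too far. What remains is that the text as printed describes change from baseline, says nothing of adjustment or constraint, and gives a power figure without naming its contrast.

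Second, the word conservative may cover more than the ICC. The effect of 0.50 in the same sentence lies below every cited effect (0.56, 0.59, and 0.68 to 0.99), and .55 may be low relative to what the adult trial found. Neither reading can be excluded, since that trial's estimates are not shown. If either was meant, the article should say so; as worded, the phrase attaches to the ICC and gives no reason.

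Third, the practical loss is modest. Even for the unconstrained contrast at ICC .55, 90 observed give 79% power at 0.56, 83% at 0.59 and 92% at 0.68. This is fair and limits the weight of the point.

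A reader might also infer that, because a three-wave average gives exactly 90, the calculation credited the effect to baseline as well and the 80% belongs to the wrong test. The article does not support that. The baseline-adjusted 8-week comparison gives the same 90, and the software settings are not reported.

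**Conclusion.** The point holds in a limited form. The power statement names no contrast. For the 8-week condition-by-time test as the Statistical Analysis section most naturally reads, 90 observed give about 70% power at d = 0.50, not 80%; 80% needs 116, and the detectable effect is about 0.57. With baseline adjustment or equal baseline means the stated figure is right (80.2% at 90), but the article does not commit to either. Under both 8-week analyses a lower ICC reduces power: at .40, 90 observed give 57% (change) or 73% (adjusted). The value of .55 therefore cannot be presented as safe merely because it is high.

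Nothing here shows that .55 is too high for this population, or which test was entered in the software. The results rest on compound symmetry, a two-sided test, d in single-wave SD units and complete data on 90.

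**What to change.** In the Sample Size section, name the contrast as the between-group difference at 8 weeks, and then do one of two things:

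- state the power with 90 observed as about 70% at d = 0.50 (or 80% at d of about 0.57) for the unconstrained condition-by-time contrast; or
- keep 80%, and state in the Statistical Analysis section that the model adjusts for baseline or constrains baseline means to be equal across arms.

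In either case, delete the word conservative for the ICC or give the reason for it. Report the required number over ICC .40 to .70 for the chosen contrast, and say that lower values reduce power.

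The cost is rewording one paragraph, plus one sentence on the model if the second option is taken. The stated power becomes less favourable or explicitly conditional. Recruitment need not change on this account.

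### The sample size does not name the contrast it powers; the 8-week condition-by-time test, as described, would need about 115 completers, not 90

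*Protocol article*

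**What the plan says.** The Sample Size section of the protocol article gives the effect size, ICC, power and alpha. The calculation was done in Optimal Design, "taking into account the multilevel analysis with a nested repeated measures design". The ICC is introduced as follows: "Using a conservative approach with intraclass correlation coefficient of .55 estimated based on our adult comorbidity trial". The result is "power calculations indicated a sample size of 90 (45 each group) would be required to detect a moderate effect size of 0.50". Power is set at 0.8 and alpha at .05 for the comparison of the two arms. The section names neither the contrast nor the number of waves entered. It then raises 90 to 122 for 35% attrition, written as 32 of 90.

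The Study Setting and Design section makes the 8-week assessment the primary end point and 6 months secondary. The Statistical Analysis section specifies a random-intercept mixed model with a dummy variable for condition. Baseline is the reference from which each participant's change is measured, and "the condition by time interaction will be examined to assess between-group differences in treatment response over time". It does not say that arm means are constrained to be equal at baseline, or that baseline is a covariate.

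**The concern.** A repeated-measures design has no single sample size. With the same effect size, ICC and alpha, the number needed depends on the contrast: an average over waves, a change from baseline, or a baseline-adjusted follow-up value. The power statement is informative only if it refers to the contrast that will be tested.

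Here the stated number agrees with contrasts that the analysis section does not describe, and falls short for the one it does. At stake is the power for each of the three primary outcomes at 8 weeks. There is also an avoidable loss of precision. Randomisation follows the baseline assessment, so the expected baseline difference between arms is zero, yet an unconstrained interaction model spends information on estimating it.

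**Working it through.** **Inputs.** From Sample Size: d = 0.50, ICC ρ = .55, alpha .05, power 0.80, 45 per arm, 35% attrition, 122 recruited. From Measures: three waves (baseline, 8 weeks, 6 months). Assumptions, because the article does not state them: a two-sided test, d in units of the single-wave SD, and the same correlation ρ between any two waves.

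**Formula.** For a contrast with variance factor f (its per-person variance relative to the single-wave variance), the total number is N = 4f(1.960 + 0.842)²/d². Power is Φ(d√(N/4f) − 1.96). The t-based versions, in brackets or in the table, are slightly more demanding.

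**Reproducing 90.**
- Difference averaged over three waves: f = (1 + 2ρ)/3 = .70, N = 88 (90 with t).
- 8-week value adjusted for baseline: f = 1 − ρ² = .6975, N = 88 (90 with t).

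Both reproduce the stated figure, so the figure alone cannot show which was used.

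**The contrast described in Statistical Analysis.** For change from baseline to 8 weeks, f = 2(1 − ρ) = .90.
- N = 4 × .90 × 7.849/.25 = 113.02, so 114 with equal arms. With t it is 115, or 116 with equal arms.
- Power with 90 completers: .5 × √(90/3.6) = 2.50, and Φ(2.50 − 1.96) = 0.705 (0.696 with t).

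**Power under attrition.** Two readings are needed, because the inflation is 90 × 1.35 = 121.5. Losing 32 of 122 leaves 90, but losing 35% of 122 leaves 79.3. That mismatch is a separate point.

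Suppose n are randomised per arm, m are followed up, and maximum likelihood keeps the baseline values of those lost. The unconstrained contrast then has variance 2[(1 − ρ²)/m + (1 − ρ)²/n].
- n = 61, m = 45: 2(.01550 + .00332) = .0376, SE .194, power 0.73.
- n = 61, m = 39.65: 2(.01759 + .00332) = .0418, SE .2045, power 0.69.
- The 79 completers alone: 0.65 (0.64 with t).

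**With baseline means constrained equal.** The variance becomes 2(1 − ρ²)/m.
- m = 45: 2(.01550) = .0310, SE .176, power 0.81 (0.80 with t).
- m = 39.65: 2(.01759) = .0352, SE .1876, power 0.76 (0.75 with t).
- In completers the variance falls by 1 − .6975/.90 = 22.5%.

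**Direction of the ICC.** Total N with equal arms, t-based, power 0.80:

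| ρ | three-wave average | change to 8 weeks | baseline-adjusted 8 weeks |
|---|---|---|---|
| .40 | 78 | 154 | 108 |
| .50 | 86 | 128 | 98 |
| .55 | 90 | 116 | 90 |
| .60 | 96 | 104 | 84 |

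If odd totals are allowed, the change contrast needs 153, 115 and 103 at ρ = .40, .55 and .60. A high ICC is the cautious choice only in the first of the three contrasts.

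**The case against.** **Origin of the 90.** A reader might infer that 90 was calculated for a difference averaged over all three waves, baseline included. Calling .55 conservative points that way, since only there does N rise with the ICC. But the section names no contrast, and a baseline-adjusted comparison gives the same 90. The origin therefore remains an inference.

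**Power of at most 0.70.** A reader might also take 0.70 as an upper limit. It is not. Maximum likelihood on all 122 gives 0.73 when 32 are lost, and the 0.64 belongs to a completer analysis that the article does not plan.

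**The interaction could be read more broadly.** The text does not spell out a single 8-week contrast. A joint 2-df test over both follow-ups, with 0.50 at each, has power 0.74 with 90 completers. Change to the mean of both follow-ups (f = .675) would need about 87 or 88. The first still falls short of 0.80. The second does not, but it is not the declared 8-week end point.

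**Parameterisation may sit in an unseen analysis plan.** This is fair: equal baseline means are neither stated nor excluded. The unconstrained model is still the natural reading, and what is raised here is disagreement between items that the article does state.

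**The effect size is cautious.** The section cites earlier effects of 0.56, 0.59 and 0.68 to 0.99. With 90 completers the unconstrained contrast would have power of about 0.79, 0.83 and at least 0.92 for these. That limits the practical harm, but the stated claim is 0.80 at 0.50.

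**Validity.** The planned interaction is a valid test. The loss is one of efficiency, and no bias is alleged.

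**Conclusion.** The point holds in a limited form. The powered contrast is not named, and the stated 90 at power 0.80 does not match the test described when that is read as an unconstrained condition-by-time contrast at 8 weeks. That contrast needs about 115 completers. Its power at d = 0.50 is about 0.70 with 90 completers, 0.73 under maximum likelihood with 32 of 122 lost, and 0.69 with 35% lost.

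These figures rest on d in single-wave SD units, a common correlation of .55 and unconstrained baseline means. They are sensitive to the correlation: about 103 are needed at .60 and 153 at .40. The documents do not support saying that 90 was definitely computed for a three-wave average, or that power cannot exceed 0.70. The shortfall is moderate, and most of it can be recovered by a change in the model.

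**What to change.** Keep the mixed model, but constrain baseline means to be equal across arms. Alternatively, enter baseline as a covariate with 8 weeks and 6 months as the outcomes. Name the 8-week between-arm difference as the primary test.

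In Sample Size, name that contrast, state the number of waves and the SD behind the 0.50, and restate the power: about 0.80 with 90 completers, and about 0.75 to 0.76 if 35% of 122 are lost. Delete the description of the ICC as conservative, and show how the number needed varies with the correlation (for this contrast 108 at .40, 90 at .55, 84 at .60).

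The cost is one line of model specification and a corrected power paragraph. No further participants, visits or data are needed.
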